#### Walking/gait tasks.

Participants will choose from a selection of music tracks that span genres including pop, rock, R&B, and country. All walks will be 1-minute in duration in a continuous 25m loop, including two 8.5m straight segments and two 4m turns, Fig 3. Walk #1 will be at the participant’s natural walking pace to calculate a baseline cadence, i.e., a walk with no cueing (NC). Walks #2, #4, and #6 will be cued, with external auditory stimuli (BPM set at +10% of baseline cadence) which are metronome (Me), instrumental music (IM), and vocal music (VM). Participants will be assigned to one of three counterbalanced cue sequences for Walks #2, #4, and #6. For example, the first participant enrolled to the study follows Sequence 1, the second follows Sequence 2, the third follows Sequence 3, and the fourth cycles back to Sequence 1, etc.

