### Outcome measures

#### Validation of gait characteristics.

This assesses the validity of CuePD to quantify PwPD gait characteristics against an established gold/reference-standard wearable (Opal). Gait characteristics include the mean, variability and asymmetry of temporal, spatial, and spatiotemporal characteristics (i.e., step time, stride time, stance time, swing time, stride length). Establishing the validity of CuePD in measuring gait characteristics is essential to accurately detect changes before and after cueing and to precisely tailor the administered cues to each individual’s physiological condition.

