#### Adherence to cues and musicality.

Adherence will be treated both as a continuous variable (percentage change in cadence from baseline) and as a binary variable for group comparisons. The primary binary adherence definition is: adherent = ≥5% increase in cadence from baseline; non-adherent = < 5%. Mann–Whitney U tests will compare Gold-MSI between adherent and non-adherent participants. Participants with missing baseline or intervention-based cadence (e.g., wishing to withdraw or technology failure) will be excluded from binary adherence analyses and numbers excluded will be reported.

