### Statistical analysis

For the first primary objective, all gait characteristics derived from CuePD and reference will be compared using ICC_2,1_ (absolute agreement), a two-way random-effects model for single measures that evaluate the absolute agreement between raters. The level of agreement will be interpreted as: < 0.5 shows poor agreement, 0.5–0.75 moderate, 0.75–0.9 good and 0.9–1.0 excellent. PCC’s will be calculated to measure the linear correlation between the two sets of results. Correlation coefficients will be interpreted as follows: zero (0), weak (±0.1 to ±0.3), moderate (±0.4 to ±0.6), strong (±0.7 to ±0.9), and excellent/perfect (+1 or −1).

The median, mean, standard deviation (SD), minimum/min, maximum/max, and standardised response mean (SRM) of cadence, stride length, gait speed and CV_stride-time_ will be calculated. These descriptive statistics will provide context for interpreting changes and help to clarify the magnitude and consistency of cueing effects. SRM allows for assessment of responsiveness and comparison of results to other studies. The SRM will be interpreted as: > 0.8 large positive response, 0.5–0.8 moderate responsiveness, and <0.5 low responsiveness where positive values imply an improvement for cadence, gait speed and stride length but negative is an improvement for CV_stride-time_, i.e., reduces variability.

To evaluate the cueing modality adherence, the percentage change in cadence from the baseline walk to each cueing modality will be calculated for each participant. The most effective cueing modality will be identified as the one producing a change closest to 10%.

Model assumptions will be formally checked, where residual normality and normality of gait characteristics within each cue condition will be assessed using the Shapiro-Wilk test, and sphericity with Mauchly’s test. The Greenhouse-Geisser correction will be applied if sphericity is violated.

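### App validity is graded only by ICC and Pearson correlation, so the plan sets no measure of the app's bias or individual error in gait units, which its stated purpose needs

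*Protocol article*

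**What the plan says.** Validation of the app's gait characteristics is the first primary objective (end of the Introduction). For it, the Statistical analysis section states that "all gait characteristics derived from CuePD and reference will be compared using ICC_2,1_ (absolute agreement), a two-way random-effects model for single measures". The ICC is graded as "< 0.5 shows poor agreement, 0.5–0.75 moderate, 0.75–0.9 good and 0.9–1.0 excellent". Correlation coefficients (abbreviated PCC, which I read as Pearson) "will be calculated to measure the linear correlation between the two sets of results" and have verbal bands of their own.

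The article names no other statistic for comparing app with reference. The medians, SDs and standardised response means in the same section describe cueing effects, and the confidence intervals mentioned later go with the cue comparisons.

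Under Validation of gait characteristics, the article says why validity matters: to detect changes around cueing accurately and "to precisely tailor the administered cues to each individual". Three other parts of the plan show what that accuracy has to serve:

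- Walking/gait tasks: "BPM set at +10% of baseline cadence". The Smartphone and CuePD section describes the server matching the music to the user's steps per minute plus 10%.
- Adherence to cues and musicality: "adherent = ≥5% increase in cadence from baseline; non-adherent = < 5" per cent.
- Statistical analysis: "The most effective cueing modality will be identified as the one producing a change closest to 10" per cent.

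**The concern.** Both validity statistics are dimensionless and scaled by the spread between participants. The same app, with the same error in seconds, scores higher in a more varied sample. Pearson correlation ignores constant and proportional bias. The absolute-agreement ICC does fall with bias, but on its own it does not say how much of the disagreement is a correctable offset and how much is scatter.

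The stated purpose concerns one person's reading: is this baseline cadence right, and is this change real? That needs error in seconds, metres or per cent. Without it, a reader told that agreement is good or excellent cannot tell whether the app is accurate enough to set a cue 10% above baseline, or to separate a 4% cadence change from a 6% one.

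**Working it through.** **Inputs.** From the article: the ICC bands (good from 0.75, excellent from 0.90), the 10% cue step, the 5% adherence cut and n = 60. The article states no error figure for the validity objective, so there is none to reproduce. It gives no between-person CV either; 5% to 20% of the mean is my assumption, shown as a range.

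**Step 1: random error only, single readings.** With no bias, the error variance per reading is (1 − ICC) × total variance. The app-minus-reference difference has twice that variance. As a percentage of the mean:

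limits of agreement = ±1.96 × √(2 × (1 − ICC)) × CV

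- ICC 0.75: 1.96 × √0.50 = 1.386, so ±1.386 × CV
- ICC 0.90: 1.96 × √0.20 = 0.877, so ±0.877 × CV

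| CV | ICC 0.75 (floor of good) | ICC 0.90 (floor of excellent) |
|---|---|---|
| 5% | ±6.9% | ±4.4% |
| 10% | ±13.9% | ±8.8% |
| 15% | ±20.8% | ±13.1% |
| 20% | ±27.7% | ±17.5% |

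**Step 2: where the limits reach 10%.** At ICC 0.75, CV = 10 / 1.386 = 7.2%. At ICC 0.90, CV = 10 / 0.877 = 11.4%.

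**Step 3: sensitivity to the definition of CV.** Step 1 takes CV from the total observed spread. If it is the spread of true values, the multiplier is 1.96 × √(2 × (1 − ICC) / ICC): 1.600 at ICC 0.75 and 0.924 at ICC 0.90. The 10% points move to 6.25% and 10.8%. The conclusion does not change.

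**Step 4: simulation.** With 60 participants, CV of true values and all error in the app, the average share of people misread by more than 10% was:

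| CV | ICC 0.75 | ICC 0.90 |
|---|---|---|
| 8% | 12.8% | 0.9% |
| 10% | 22.4% | 3.7% |
| 15% | 41.6% | 16.5% |
| 20% | 54.2% | 30.0% |

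**Step 5: bias only.** If every reading is shifted by b and there is no scatter, ICC = s² / (s² + b²/2), where s is the between-person SD. Hence b = s × √(2 × (1 − ICC) / ICC). At ICC 0.90 this is 0.471 SD: 4.7% of the mean at CV 10% and 9.4% at CV 20%. Pearson r is 1 throughout. The gap between 0.90 and 1 reveals an offset but does not give its size in gait units.

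**Step 6: change from baseline.** The 5% cut and the 10% target apply to percentage change within a person, not to single readings. If the app reads a constant multiple c of the truth for a person, (c × cue − c × baseline) / (c × baseline) equals the true percentage change, so that error cancels exactly. A stable additive error largely cancels. Walk-to-walk random error does not. If the app-minus-Opal differences on two walks have equal variance and correlation ρ, the change-score limits are roughly the level limits × √(2 × (1 − ρ)): wider than the level limits when ρ is below 0.5, narrower when it is above. The article gives no ρ, so the table above cannot be read against the 5% cut. Change-score limits have to be estimated directly.

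**The case against.** The strongest reply has four parts.

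**The ICC form is a sound choice.** Absolute agreement penalises bias, and paired with Pearson it separates systematic from random disagreement to some extent. This stands. A reader might infer that a constant offset would go unnoticed, or that Pearson should be removed. Neither follows: an ICC clearly below Pearson signals an offset. What is missing is its size.

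**Excellent need not mean poor accuracy.** A reader might infer that either grade lets the app misread a person by 10%. The cue step is on cadence, so step or stride time is the relevant measure. With an assumed stride-time SD of 0.10 s on 1.1 s (CV about 9%), ICC 0.90 gives ±0.924 × 0.10 = ±0.092 s, or ±8.4%, and that is the bottom of the band. Stride length, with an assumed 0.20 m on 1.2 m, gives ±0.185 m (15%), but no cue or adherence rule uses stride length. At CV 5%, excellent gives ±4.4%. This stands, and the point for excellent is conditional on the CV.

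**No pass mark is stated.** A reader might infer that the objective could be declared met by an inaccurate app. The bands are descriptive, and the Discussion puts estimation ahead of formal testing and urges caution over variability and asymmetry. This stands too.

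**It is an article, and a fuller plan may add error measures.** That is possible. But the article does not leave this analysis open: it names the model, the agreement type and the grading bands for a primary objective. The point is that this grading does not fit the purpose stated beside it.

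**Conclusion.** The point holds in a limited form. The plan grades app validity only by two statistics that depend on between-person spread, and it prespecifies no bias or individual error in gait units, although detecting change and tailoring cues to each person require it.

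Over an assumed CV of 5% to 20% with purely random error, good (ICC 0.75) is compatible with limits of about ±7% to ±28%, and excellent (ICC 0.90) with about ±4% to ±18%. Error on a single reading reaches the cue step at a CV of about 7% for good and about 11% for excellent. These are errors the band floors permit, not forecasts of the app's performance.

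The documents do not support saying that app error exceeds the 5% adherence cut. That cut applies to change scores, in which stable error largely cancels, and the part that remains is unknown. This should be changed, but it does not invalidate the design.

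**What to change.** For each validated characteristic, add to the Statistical analysis section:

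- the mean app-minus-Opal difference with its 95% CI and the 95% limits of agreement, in units and as a percentage of the mean, by a method that allows for repeated walks per person;
- the same quantities for app versus Opal change from baseline.

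State how they will be read. The level limits for cadence (or step time) bear on the accuracy of the baseline cadence used to set the cue. The change-score limits for cadence (or step time) are read against the 5% adherence cut and the 10% target. Keep ICC(2,1) as the relative measure. Pearson may stay as a supplement but should not be presented as evidence of agreement.

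The change is to analysis wording only and uses paired data that will be collected anyway. The cost is somewhat more reporting and, possibly, less flattering results.

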A two-way mixed ANOVA will be used to assesses the effects of cueing modality and walk order on outcomes, i.e., cadence, gait speed, stride length, and CV_stride-time_. Comparable to the referenced PD study, cueing modality will be modelled as a within-subject factor, while walk order as a between-subject factor to account for potential sequence effects. For each outcome, within-participant changes from baseline will be calculated using cue-specific difference scores. To account for differences in scale and statistical distribution among the outcomes, change scores will be computed using Equations (30)-(31):

Percentage change of gait speed and stride length from baseline, calculated as:

$$\%\Delta =\frac{\text{Cue Value}-\text{Baseline Value}}{\text{Baseline Value}}\times \text{1}\text{0}\text{0}$$
(30)

In contrast,${\text{ CV}}_{\text{stride}-\text{time}}$, a dimensionless ratio-based variable that may have a skewed distribution, change will be computed using the natural log-ratio of cue value to baseline:

$$\Delta_{log}=\text{log}\left(\text{Cue Value}+\in \right)-\text{log}\left(\text{Baseline Value}+\in \right)$$
(31)

where 𝜖 is a small constant to avoid the logarithm of zero. This transformation was chosen as ${\text{CV}}_{\text{stride}-\text{time}}$ is a ratio-based measure that can be highly skewed and exhibit unequal variances across conditions. Applying the *log* transformation to change scores helps to normalise the distribution and stabilise the variance, thereby supporting more reliable statistical comparisons of cueing effects on ${\text{CV}}_{\text{stride}-\text{time}}$ in this within-subjects design. Post-hoc comparisons between cueing modalities will be conducted using paired t-tests, with Bonferroni correction applied to account for multiple comparisons. Effect sizes will be reported using Cohen’s d.

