If assumptions for normality are not met, a Friedman test will be used to assess within-subject differences across cueing conditions. Post-hoc Wilcoxon signed-rank tests, with Bonferroni correction, will be conducted only if the Friedman test is statistically significant. For between-subject effects (e.g., walk order), where normality assumptions are violated, the Kruskal–Wallis test will be used to assess group-level differences between walk-order groups. Interaction effects between cueing and walk order will be explored non-parametrically by conducting separate Friedman tests within each walk order group. Effect sizes for non-parametric tests will be calculated using the rank-biserial correlation coefficient, $\text{r}=\text{Z}/\sqrt{\text{N}}$, providing a measure of the magnitude of the effects observed.

For the three primary comparisons, we will control the familywise error rate using a Bonferroni adjustment. Given three cueing modalities, statistical significance (*p*) will be evaluated at a two-sided α = 0.01/3 = 0.0033. Effect sizes (i.e., SRM) and 95% confidence intervals will also be reported. Secondary and exploratory analyses (e.g., comparing cueing modalities to one another, examining washout effects, assessing stride-to-stride variability) will not be subject to multiplicity correction. For these analyses, a two-sided *p*-value of 0.05 will be considered statistically significant across all parametric and nonparametric tests.

To assess whether the first cue produced short-term residual effects, we will calculate changes in gait outcomes from baseline to each cued walk and from each cued walk to its subsequent washout walk (WO1 and WO2). For each cue exposure, a carryover score will be calculated as the difference between the change induced by the cue and the change observed during the corresponding washout period, reflecting retained cue effects. The approach enables an evaluation of carryover effects after each cued walk separately, thereby capturing any cumulative or progressive retention of cueing effects. Group differences based on initial cue type (i.e., counterbalanced sequence) will be evaluated using one-way ANOVA or the Kruskal–Wallis test, depending on normality assumptions [74–80].

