### Primary objectives: Validity and evaluating the effects of personalised auditory cues on gait

The impact each personalised auditory cue has on participants’ stride length, gait speed, and${\text{ CV}}_{\text{stride}-\text{time}}$ are a significant exploratory interest. These metrics, in particular${\text{ CV}}_{\text{stride}-\text{time}}$, where a decrease is known to reduce the risk of falling, have indicated variable effects among PwPD in other cueing-related studies, particularly where music cueing is not personalised [9,44,73]. The findings from this study will establish a baseline understanding of their (i) validity (from an app and smartphone worn on the lower back) and (ii) whether personalised cues can consistently reduce stride variability across a broader range of participants.

Observed gait responses will be interpreted in the context of sequence-conditional effects (cue order, exposure, and adaptation over time), and not as definitive evidence of causal superiority of one cueing condition over another. Analyses of gait variability and asymmetry will be interpreted cautiously, as these measures typically exhibit greater dispersion and may be underpowered (as sample size of based on gait speed). Emphasis will be placed on estimating effect sizes and examining consistency of responses across conditions, rather than on formal hypothesis testing.

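### The SRM bands are signed cut-offs that cannot grade an improvement in stride-time variability or a deterioration in the other outcomes, and the non-parametric effect size is misnamed

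*Protocol article*

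**What the plan says.** All wording is in the protocol article.

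- **SRM bands** (Statistical analysis). The SRM is to be calculated for cadence, stride length, gait speed and CV of stride time. The top band is set first: "The SRM will be interpreted as: > 0.8 large positive response". A middle band, graded as moderate, runs from 0.5 to 0.8. The lowest band is then given together with the sign convention: "and <0.5 low responsiveness where positive values imply an improvement for cadence, gait speed and stride length but negative is an improvement for". The outcome that completes this clause is the CV of stride time.
- **Sign of the CV change score** (same section, Equation 31). For this outcome "change will be computed using the natural log-ratio of cue value to baseline", that is, log cue value minus log baseline value. A fall in variability is therefore negative, in line with the sign clause.
- **Role of the SRM.** The section introduces it among descriptive statistics that give context, and later names it as the effect size to be reported, alongside 95% confidence intervals. The Discussion, under the heading on primary objectives, adds: "Emphasis will be placed on estimating effect sizes and examining consistency of responses across conditions, rather than on formal hypothesis testing".
- **Non-parametric effect size** (Statistical analysis). "Effect sizes for non-parametric tests will be calculated using the rank-biserial correlation coefficient", with the formula given as r = Z/√N. The same paragraph uses Friedman, Wilcoxon signed-rank and Kruskal–Wallis tests.

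**The concern.** The SRM rule does two jobs in one sentence: it grades size and it assigns direction. The direction part covers both signs. The size part covers only positive values, because everything below 0.5, including every negative number, drops into the lowest band. The label on the top band also contains the word positive, which does not suit an outcome where improvement is negative. The correlation bands earlier in the same section carry ± signs, so the SRM bands differ in form from their neighbour.

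This matters because the abstract sets out to describe both beneficial and non-beneficial responses and allows for adverse effects, yet the bands have no grade for the size of an adverse response in cadence, gait speed or stride length. For CV of stride time the plan itself expects low power and leans on effect sizes, so the grade is likely to be quoted in the results.

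The second problem is one of identity. A reader who sees a value reported as a rank-biserial correlation will take its limits to be ±1 and compare it with values from other studies on that scale. The printed formula does not give that quantity, and it cannot be applied directly to two of the three tests in its paragraph.

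**Working it through.** **1. SRM bands**

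The plan gives no figure to reproduce, so the check is to apply the printed rule. Inputs: cut-offs of 0.8 and 0.5, and the stated sign convention (positive is improvement for cadence, gait speed and stride length; negative is improvement for CV of stride time). The SRM is taken in its usual form, mean change divided by SD of change, with change as cue minus baseline.

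| SRM | Band as printed | CV of stride time, bands on abs(SRM) | Gait speed, stride length or cadence, bands on abs(SRM) |
|---|---|---|---|
| −0.9 | low | large improvement | large worsening |
| −0.65 | low | moderate improvement | moderate worsening |
| −0.3 | low | low improvement | low worsening |
| +0.3 | low | low worsening | low improvement |
| +0.65 | moderate | moderate worsening | moderate improvement |
| +0.9 | large positive | large worsening | large improvement |

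The printed band is too low in the rows at −0.9 and −0.65, for all four outcomes. At +0.9 the size is right for CV of stride time, but the word positive sits on a worsening. At −0.3 the printed grade is correct on either reading.

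**2. Rank-biserial correlation against Z/√N**

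Inputs: n = 54 pairs (the single-comparison figure under Sample size, and also 60 × 0.9) and n = 60 (planned recruitment). Assumptions: N is the number of pairs, there are no ties or zero differences, and no continuity correction is used.

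Take the extreme case where every pair changes in the same direction.

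- Matched-pairs rank-biserial = (sum of positive ranks − sum of negative ranks) / (sum of all ranks) = 1.00.
- Z = [n(n+1)/4] / √[n(n+1)(2n+1)/24].
- n = 54: numerator 54 × 55/4 = 742.5; variance 54 × 55 × 109/24 = 13,488.75; SD 116.14; Z = 6.39; Z/√54 = 6.39/7.35 = **0.87**.
- n = 60: numerator 60 × 61/4 = 915; variance 60 × 61 × 121/24 = 18,452.5; SD 135.84; Z = 6.74; Z/√60 = 6.74/7.75 = **0.87**.

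The gap is not confined to the extreme case. Both statistics are proportional to the difference between the positive and negative rank sums, so their ratio is fixed for a given n: √[1.5(n+1)/(2n+1)]. At n = 54 this is √(82.5/109) = 0.87, and at n = 60 it is √(91.5/121) = 0.87. Under the assumptions above, Z/√N is always about 13% smaller than the rank-biserial value.

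For the omnibus tests, Friedman across three cues and Kruskal–Wallis across three sequence groups each produce a chi-square-type statistic on two degrees of freedom. There is no Z to put into the formula.

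**The case against.** The strongest reply is that the SRM sentence, read to its end, is clear enough. It says which sign is improvement for each outcome, and Equation 31 uses the same orientation. Words such as moderate and low describe magnitude, so the natural reading is size bands with direction taken from the sign. Much of this stands. A reader might infer that the rule swaps benefit and harm; it does not, because the sign clause makes −0.9 an improvement and +0.9 a worsening for CV. A reader might also infer that every CV improvement is misgraded; those between 0 and −0.5 are rightly low.

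Nor do the documents support the claims that the bands are the trial's main readout or that they conceal harm. Signed SRMs with confidence intervals, means, medians, SDs and ranges are all to be reported. Assessment of stride-to-stride variability is listed among the secondary and exploratory analyses, the trial is sized on gait speed, and no test depends on the verbal grade.

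What the reply does not remove is the gap in the size rule. The sign clause supplies direction only; it provides no moderate or large grade for any negative value. Reading the bands as absolute values is a sensible repair, but it is not printed, and the top band's label works against it.

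On the non-parametric measure, it can be said that the formula is given, so for Wilcoxon tests the quantity computed is unambiguous and only its name is wrong. It is also a fallback, used only if normality fails. An article may fairly leave effect sizes for omnibus tests to a fuller plan. All that is fair, but the article does state a rule for non-parametric tests in general, and that rule is wrong in name for one test and unusable as stated for two.

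**Conclusion.** The point holds as two minor errors in reporting rules.

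- **SRM bands.** Direction is stated and is not reversed. The size grading fails for every SRM at or below −0.5: a moderate or large CV improvement, and a moderate or large deterioration in cadence, gait speed or stride length, is graded low. A CV worsening above 0.8 meets the cut-off whose label reads as favourable.
- **Non-parametric effect size.** Z/√N is not the rank-biserial correlation. It is about 13% smaller at 54 to 60 pairs, with a ceiling of about 0.87 instead of 1.00, assuming N counts pairs and there are no ties or zero differences. It cannot be obtained directly from the Friedman or Kruskal–Wallis statistics.

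These affect the labels and values of effect sizes. They do not alter any hypothesis test, p-value or confidence interval for the SRM.

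**What to change.** In the SRM sentence, state that the bands apply to |SRM|, drop the word positive from the label of the top band, and report improvement or deterioration separately under the sign convention already given. Reversing the sign for CV of stride time, so that positive always means improvement, would be a helpful addition but does not by itself grade deteriorations.

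In the non-parametric sentence, for Wilcoxon signed-rank tests either compute the matched-pairs rank-biserial from the rank sums, or keep Z/√N and call it r, saying that N is the number of pairs. Limit the sentence to those tests. For the omnibus tests name a suitable measure, for example Kendall's W for Friedman and epsilon-squared for Kruskal–Wallis.

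The cost is a few sentences and small changes to the reporting code. No new data are needed, and neither the sample size nor any test changes.

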#### Impact of cueing.

This examines the ability of different personalised auditory cues to modify/retrain gait in PwPD. By comparing the effects of metronome beats, instrumental music, and vocal music on gait speed, stride-time variability, and stride length, this outcome seeks to identify which auditory cues most effectively enhance gait stability and performance. ${\text{Coefficient of variance of stride}-\text{time }(\text{CV}}_{\text{stride}-\text{time}})$ will be calculated as the standardised measure of the dispersion of stride times. This provides a more reliable measure of stride-time variability and has shown to be a significant indicator of gait instability and an independent predictor of fall risk among older adults and PwPD, underscoring its importance in clinical and rehabilitative settings [73]. Measuring changes in gait will be key to assessing CuePD as a gait retraining tool.

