#### Sample size.

Sample size calculations were based on detecting changes in gait speed using a within-subject design. Assuming a standardised response mean (SRM) of 0.5 (moderate effect size) for gait speed, a two-sided significance level (α) of 0.01, and 90% power, approximately 54 participants would be required to detect a statistically significant change in gait speed for a single comparison (e.g., cued vs. non-cued walking). When accounting for the three cueing conditions and the associated adjustment for multiple (three) comparisons, we applied a Bonferroni correction resulting in an adjusted alpha of α (0.01/3 = 0.0033). That requirement increases sample size to approx. 55 participants. However, to allow for an anticipated attrition rate of up to 10%, we plan to recruit 60 participants in total. This sample size ensures adequate power to detect moderate cueing effects on gait speed, accommodates potential dropouts, and provides balanced representation across randomisation sequences.

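### The rule naming the 'most effective' cue as the one with cadence change nearest +10% always names one, and no planned test or interval controls the label

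*Protocol article*

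**What the plan says.** The Statistical analysis section treats cue adherence in a short paragraph. First, "the percentage change in cadence from the baseline walk to each cueing modality will be calculated for each participant". Then comes the selection rule: "The most effective cueing modality will be identified as the one producing a change closest to 10" per cent. The target comes from the Walking/gait tasks section, where the cued walks have "BPM set at +10% of baseline cadence) which are metronome (Me), instrumental music (IM), and vocal music (VM").

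Three other places bear on the rule:

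- The same section plans formal comparisons that include cadence: "A two-way mixed ANOVA will be used to assesses the effects of cueing modality and walk order on outcomes, i.e., cadence, gait speed". The other outcomes listed are stride-time variability and stride length. Post-hoc paired comparisons and non-parametric fallbacks follow.
- It later classes comparisons between cues as secondary or exploratory: "Secondary and exploratory analyses (e.g., comparing cueing modalities to one another, examining washout effects, assessing stride-to-stride variability) will not be subject to multiplicity correction".
- The Discussion, under the primary objectives, says gait responses will be read "not as definitive evidence of causal superiority of one cueing condition over another", with the emphasis on effect sizes and consistency.

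The rule does not say whether the change it ranks is a group mean, a median or a count over participants.

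**The concern.** The rule picks the smallest of three observed distances from 10%. Three distances always have a smallest one, barring exact ties, so a cue is called most effective whatever the data show. That includes the case where the cues are equal and the case where none of them changes cadence. A lead of a few tenths of a point that is pure noise would be reported in the same words as a real difference.

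The planned analyses of cadence do not prevent this. Nothing makes the label depend on their result. They also ask a different question: true changes of 7% and 13% differ in the ANOVA, yet both lie 3 points from the target and tie under the rule. Finally, naming a most effective cue fits poorly with a Discussion that disclaims definitive superiority of any cue.

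**Working it through.** The protocol gives no error rate for this rule, so there is no figure to reproduce. The rule was simulated.

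**Inputs from the protocol**

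- Three cues and a target of +10%.
- Sample size: "to allow for an anticipated attrition rate of up to 10%, we plan to recruit 60 participants in total". With 10% lost, 60 × 0.9 = 54 completers.

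**Assumed, because the protocol gives no value**

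- SD of the within-person difference between two cues' cadence changes: 3, 5 or 8 percentage points.
- The ranked change is the group mean, and the data are normal.

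**Rule:** winner = the cue with the smallest |mean change − 10|.

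**Precision of a difference between two cue means:** SE = SD / √54, with √54 = 7.35. This gives 3/7.35 = 0.41, 5/7.35 = 0.68 and 8/7.35 = 1.09 points.

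**Three equal cues (all 0% or all 7%)**

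| SD of difference | A cue is named | Each cue wins | Median lead over runner-up |
|---|---|---|---|
| 3 | 100% | about 33% | 0.20 points |
| 5 | 100% | about 33% | 0.33 points |
| 8 | 100% | about 33% | 0.53 points |

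A separate simulation used correlated changes (SD of change 4, 6 or 10 points, correlation 0.3 to 0.7) and true changes of 0%, 5% or 10% for all cues. It also named a cue every time, with each winning 31% to 35% of the time and median leads of 0.16 to 0.66 points. A repeated-measures F test of cadence at 0.05 on the same data was significant in 4.3% to 5.4% of trials. So about 95% of the named cues had no support from a test of the kind the plan itself schedules. Ranking on mean absolute individual deviation gave the same one-third split.

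**One cue truly nearer the target (7, 7 and 8%)**

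| SD of difference | Right cue named | Wrong cue named |
|---|---|---|
| 3 | 0.986 | 1 − 0.986 = about 1% |
| 5 | 0.878 | 1 − 0.878 = about 12% |
| 8 | 0.715 | 1 − 0.715 = about 29% |

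A hand check agrees. The chance that one given wrong cue beats the right one is Φ(−1/SE): Φ(−2.45) = 0.007, Φ(−1.47) = 0.071 and Φ(−0.92) = 0.179. Doubling for two wrong cues gives upper bounds of 1.4%, 14% and 36%, and the simulated rates lie at or below them. Repeating the simulation with correlation 0.5 between the changes left these rates unchanged to the nearest percentage point.

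**The case against.** The best defence is that this is a descriptive step in a secondary adherence summary. Any ranking of point estimates produces a first place, and that harms only if it is read as inference. The plan also reports SDs, SRMs and 95% intervals, tests cadence between cues, and limits interpretation in the Discussion. Much of this stands, and it is why the point is minor. It does not repair the rule. The sentence is unconditional, and neither the tests nor the caveat changes when the label is applied. A reader who supposed that the tests do control it could not tell at what level: the post-hoc comparisons between cues are Bonferroni-corrected in one place, while comparisons between cues are exempt from correction in another.

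Four stronger readings are tempting but not supported:

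- *That the plan never tests cadence between cues.* It does. The gap is that those tests neither control the label nor address distance from 10%.
- *That this rule answers the aim in the Impact of cueing section.* There, "this outcome seeks to identify which auditory cues most effectively enhance gait stability and performance", but the outcomes named are gait speed, stride-time variability and stride length, not cadence.
- *That the winner will decide which cue the app favours.* Nothing in the protocol says so.
- *That the Discussion flatly contradicts the rule.* It disclaims definitive evidence of superiority, and a nominal ranking can be read under that caveat. The two are in tension over wording.

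**Conclusion.** The point holds as a minor one. As written, the rule labels one cue most effective in every trial, including trials with three equal cues or with no effect on cadence. This follows from the wording and needs no assumed SD when group means are ranked, because exact ties are then negligible. Rounded medians or participant counts could tie, and the protocol gives no outcome for that.

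The sizes do rest on assumptions: 54 completers, group means, normal data and difference SDs of 3 to 8 points. At an SD of 3 the rule rarely picks wrongly when one cue is a full point nearer the target (about 1%). At 8 it does so in more than a quarter of trials. Rates for true changes that straddle the target should not be quoted as the size of the problem, because they depend heavily on the unknown correlation. For 9, 10 and 11%, wrong naming is about 3%, 22% and 45% with independent changes, and about 17%, 43% and 59% at correlation 0.5. The primary comparisons and the sample size do not use this rule.

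**What to change.** Replace the selection sentence with:

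> Cues will be ranked descriptively on closeness to the +10% cadence target, using each participant's absolute deviation from +10% (as defined for the Gold-MSI analysis), with paired between-cue differences and 95% confidence intervals. Where an interval includes zero, those cues will be reported as not distinguished.

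Drop 'most effective' from this paragraph.

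The change affects wording and analysis only and uses data already collected. It has three costs:

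- The quantity ranked becomes the individual absolute deviation, and the plan should say so openly. The protocol already uses this measure for the Gold-MSI correlations, and it avoids a fault of group means: if half the participants changed by 0% and half by +20%, the mean would be exactly 10% although every participant was 10 points off target.
- The trial will often report that the cues are not distinguished.
- Three unadjusted intervals can together mislead in up to 3 × 5% = 15% of trials with equal cues, so they should be presented as descriptive.

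A stricter decision rule is not advised. Requiring Bonferroni-adjusted intervals against both other cues to exclude zero would name the truly nearer cue (7, 7 and 8%) in only about 24%, 3% and 0.5% of trials at SDs of 3, 5 and 8.
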